#### Dysphagia severity assessment via FEES

Dysphagia severity is evaluated using following dysphagia scores:Secretion Severity Rating Scale (SSRS): this 4-point scale assesses the patient’s ability to manage saliva and secretions, which correlates with the risk of aspiration pneumonia. Higher scores on this scale indicate a greater risk of aspiration pneumonia and respectively more severe dysphagic symptoms [32].The Penetration-Aspiration Scale (PAS): This 8-point scale evaluates the extent of penetration and aspiration of saliva, liquids and food. It also describes the patient’s sensory response to penetration or aspiration and their ability to expectorate the penetrated or aspirated material [30]. Higher scores on this scale indicate more severe dysphagic symptoms with PAS-scores 6–8 indicating different severities of aspiration.Yale Pharyngeal Residue Severity Scale (YS): A 5-point scale that measures the severity of residue in the hypopharynx after swallowing saliva, food and liquids [31]. Higher scores on this scale indicate more severe dysphagic symptoms.Functional Oral Intake Scale: Following each FEES assessment, the patient’s ability to orally intake liquids and food is measured by the 7-point Functional Oral Intake Scale (FOIS-G, German version [33]). Lower scores on this scale indicate a deterioration in oral intake ability, with levels 1–3 corresponding to various levels of non-oral feeding and levels 4–7 corresponding to different levels of oral feeding [33, 34].

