## Outcomes

### Primary outcome

The primary outcome will assess the impact of the type and form of anaesthesia (intravenous vs. local) administered during TEE on swallowing in patients with ischaemic stroke and TIA, based on the aforementioned dysphagia scores [30–34].

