### Sample size estimation

Given the lack of existing data on the influence of anaesthesia type and form during TEE on swallowing in ischaemic stroke and TIA patients, this study is designed as a pilot trial. A total of 50 participants will be enrolled, with 25 patients in each group (stroke vs. TIA). The primary aim of this exploratory phase is to gather preliminary data to estimate effect sizes. These estimates will then serve as the basis for a formal power calculation and definitive sample size planning for a subsequent full-scale study.

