### Definition of dysphagia

Dysphagia is determined with the following cut-off values of the dysphagia scores:

Secretion Severity Rating Scale for Saliva Management (SSRS): SSRS ≥ 1; Penetration Aspiration Scale (PAS): PAS ≥ 3; Yale Pharyngeal Residue Severity Rating Scale: YS ≥ 3; Functional Oral Intake Scale (FOIS-G): FOIS-G < 7. Differences in patient-related data between the two groups: dysphagia/non-dysphagia group and intravenous vs. oral anaesthesia group are tested using Pearson’s chi-square test, Fischer’s exact test, *t*-test for independent samples or the Mann–Whitney *U*-test. For the purpose of logistic regression analyses, we intend to apply a median split to dichotomize the SSRS, PAS, YS and FOIS-G scores and create a binary outcome variable.

Assumptions for a *t*-test for independent samples are tested with the Levent test for variance homogeneity and the Shapiro–Wilk test including visual inspection of thedistribution plots for the assessment of normal distribution. If there is no homogeneity of variance or normal distribution, the Mann–Whitney *U* test for group differences is used. Correlations are calculated using the Pearson product-moment correlation or the Spearman rank correlation.

The inter-rater reliability between two raters is determined using a linearly weighted Cohen’s kappa, as this takes into account matches that could have arisen by chance on the one hand and places more weight on high non-matches on the other [39]. Furthermore, the percentage agreement and the Spearman rank correlation are specified for the agreement between two raters. In the case of a calculation of inter-rater reliability with more than two raters, a general agreement of all raters including subtraction of agreements by chance is calculated using Fleiss kappa [39].

Effect sizes are given according to Cohen’s d with a 95% confidence interval. *p*-values are given for all statistical results. The criterion for statistical significance is set at *p* < 0.05. Conclusions about clinically, practically and scientifically relevant correlations or differences are not made solely on the basis of the defined statistical significance [40].

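### Cohen's d is the only effect size named for group differences, but the primary outcome is scored on short ordinal scales, so d alone does not match the planned analyses and can mis-size the follow-up study

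*Protocol article*

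**What the plan says.** The Primary outcome section reads: "The primary outcome will assess the impact of the type and form of anaesthesia (intravenous vs. local) administered during TEE on swallowing", judged on the dysphagia scores. The section Dysphagia severity assessment via FEES describes these as short graded scales:

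- SSRS: "this 4-point scale assesses the patient’s ability to manage saliva and secretions"
- PAS: "This 8-point scale evaluates the extent of penetration and aspiration of saliva, liquids and food"
- Yale scale (YS): "A 5-point scale that measures the severity of residue in the hypopharynx after swallowing saliva, food and liquids"
- FOIS-G: "measured by the 7-point Functional Oral Intake Scale"

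The section Definition of dysphagia holds most of the statistical methods. It gives cut-offs for dysphagia (for PAS, a score of 3 or more) and lists chi-square, Fisher, t and Mann-Whitney tests. It then sets the rule: "If there is no homogeneity of variance or normal distribution, the Mann–Whitney *U* test for group differences is used". It also plans logistic regression after a median split of the four scores. On effect measures for group differences it has one sentence: "Effect sizes are given according to Cohen’s d with a 95% confidence interval".

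The section Sample size estimation explains why this matters: "The primary aim of this exploratory phase is to gather preliminary data to estimate effect sizes". Those estimates are to feed the power calculation of a full-scale study. The Interim analysis section repeats the focus on effect sizes.

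**The concern.** Cohen's d is a difference in means divided by a pooled standard deviation. On a graded scale it treats all steps as equal, so one patient moving from PAS 1 to PAS 8 counts as much as seven patients moving from PAS 1 to PAS 2. A Mann-Whitney test responds to something else: the probability that a patient in one group scores higher than a patient in the other, counting ties as half. A logistic model on a dichotomised score estimates an odds ratio.

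When scores pile up at the normal end of the scale, these quantities can diverge widely. Reporting d alone then hides which patients got worse and by how much. A sample size computed from d can also be far from what a rank or binary analysis needs. Since the pilot exists to supply effect sizes, the weakness falls on its main deliverable.

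**Working it through.** The plan has no figure to reproduce: the 50 patients are a pilot choice without a power calculation. The check asks two things: which test the plan's rule would select, and how far sizing from d can depart from sizing for that test.

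**Inputs.** From the protocol: the scale lengths, the PAS cut-off of 3, and significance at p < 0.05. Assumed, because the documents do not give them: two-sided testing, 80% power, 1:1 allocation, and all score distributions. The reference PAS distribution for levels 1 to 8 is 60/20/8/3/3/2/2/2%.

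**Which test the rule selects.** In simulated samples of 25, Shapiro-Wilk rejected normality in 99% to 100% of cases for skewed PAS, SSRS and FOIS-G scores, and in 94% for a bell-shaped 5-level Yale score. Rejection was less frequent for an 8-level score spread evenly over all levels (63%), and in groups smaller than 25. For skewed or very short scales the t-test would rarely survive the plan's own check.

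**Formulas.**

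- d = mean difference / √((variance 1 + variance 2)/2)
- P = P(higher score) + ½ P(tie)
- n per group from d = 2(1.96 + 0.84)²/d²
- n per group for Mann-Whitney = (1.96 + 0.84)²(1 − T)/(6(P − 0.5)²), where T is the sum of the cubed level proportions averaged over both groups

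With unrounded normal quantiles, (1.96 + 0.84)² is 7.849. The reference group has mean 1.93 and variance 2.605.

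**Pattern A: 8% of patients move from PAS 1 to PAS 8.**

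- Mean difference: 0.08 × 7 = 0.56. The new variance is 5.170 and the pooled SD 1.972, so d = 0.56/1.972 = 0.284.
- P = 0.5 + 0.08 × (0.99 − 0.30) = 0.555. Here 0.99 and 0.30 are the chances, with ties as half, that PAS 8 and PAS 1 exceed a reference patient.
- n from d: 15.70/0.284² ≈ 195.
- n for Mann-Whitney, with T = 0.184: 7.849 × 0.816/(6 × 0.0552²) ≈ 350.
- PAS ≥ 3 rises from 20% to 28%.

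**Pattern B: 40% of patients move from PAS 1 to PAS 2.**

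- Mean difference: 0.40 × 1 = 0.40. The new variance is 2.101 and the pooled SD 1.534, so d = 0.40/1.534 = 0.261.
- P = 0.5 + 0.40 × (0.70 − 0.30) = 0.660.
- n from d: 15.70/0.261² ≈ 231.
- n for Mann-Whitney, with T = 0.129: 7.849 × 0.871/(6 × 0.16²) ≈ 45.
- PAS ≥ 3 stays at 20%.

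**Power of Mann-Whitney at the d-based size.** Pattern A: 2.80 × √(195/350) − 1.96 = 0.13, which is about 55% power; simulation gives 53% to 56%. Pattern B: practically 100%. The target was 80%.

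**Proportional-odds shift from the same reference distribution.**

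| Odds ratio | d | P | n per group from d | n per group, Mann-Whitney | Ratio |
|---|---|---|---|---|---|
| 2 | 0.324 | 0.597 | 149.6 | 118.2 | 1.27 |
| 2.5 | 0.437 | 0.630 | 82.2 | 67.4 | 1.22 |
| 3 | 0.532 | 0.657 | 55.4 | 47.1 | 1.18 |

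Here d errs on the large side, by 18% to 27%.

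**The case against.** The strongest reply has four parts.

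**The examples are extreme and assumed.** Patterns A and B are chosen shifts on a distribution that is not in the documents. Under a proportional-odds shift, d gives a similar and somewhat conservative sample size. This stands, and it limits the point: d can mislead, but it does not always do so. A reader might infer that d cannot describe the effect or size the next study at all; the table above does not support that. Nor do A and B show the same d for opposite effects: both are worsenings, and they differ in shape, not direction.

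**The text does not strictly exclude other measures or tie the next study to d.** The t-test is formally the first option. The list of tests is worded for patient characteristics rather than for the graded scores. A logistic model ordinarily yields odds ratios, and no test is named for the full-scale study. This stands in part. It rules out saying that the next sample size will be wrong. It does not change the fact that the one effect measure the plan names for group differences is a standardised mean difference, with no conversion given.

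**Other analyses have their own measures.** A reader might infer that the correlations and the rater agreement are left with p-values only. They are not: the plan specifies correlation coefficients, weighted and Fleiss kappa and percentage agreement. Their confidence intervals are detail that an article may leave to the analysis plan.

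**Imprecision dominates.** With an assumed 25:25 split by anaesthesia, the 95% CI around a d near zero is about ±1.96 × √(50/625) = ±0.55. This is true, and any measure from 50 patients will be imprecise. But imprecision is not a reason to report a measure that also does not match the analysis.

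**Conclusion.** The point holds in a limited form. Cohen's d is the only effect size named for group differences, while the primary outcome rests on ordinal scores of 4, 8, 5 and 7 levels. For these the plan's own rules lead mostly to a rank test or a dichotomised model. Used alone, d does not match those analyses.

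The size of the problem depends on the shape of the effect. In the two non-proportional patterns, sizing from d gave 0.56 times (195 against 350) and 5.2 times (231 against 45) the number that Mann-Whitney needs. Under proportional odds it gave 1.18 to 1.27 times that number. All of this rests on assumed distributions, two-sided 5% testing, 80% power and equal groups. The documents give no score distribution and no split by anaesthesia type, so which case applies is unknown. This should be corrected, because effect sizes are the pilot's stated main product, but it does not invalidate the pilot.

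**What to change.** Replace the single sentence on effect sizes with wording along these lines:

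- For graded FEES scores, report the Mann-Whitney probability (higher score plus half of ties) or a proportional-odds ratio, with a 95% CI.
- For dysphagia yes/no, report the risk difference and the odds ratio, each with a 95% CI.
- Tabulate the full distribution of each score by anaesthesia group, so that a later team can size any test from it.
- Keep Cohen's d with its CI for roughly continuous variables such as TEE duration.
- State that the next study's sample size will be based on the ordinal or binary measure that matches its planned test.

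The cost is a change of wording and slightly more reporting from standard software. No extra patients, visits or data are needed.

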### Interim analysis

An interim analysis will be conducted after the enrollment of 25 patients in each group. This analysis is intended solely for exploratory purposes and will focus on estimating effect sizes. No formal stopping rules are defined.

### Study quality control

All measurement instruments used in this trial have been examined and demonstrate excellent validity and reliability [30–32, 38]. As university hospital, UKGM is best qualified in conducting research. All investigators have been trained in the assessment tools and interventions being evaluated.

## Discussion

This protocol presents a pilot prospective single-blinded controlled study designed to assess further risks of dysphagia following TEE. The trial aims to address several outcomes which will be correlated with the severity of dysphagia after TEE, building on the findings from the initial trial.

The initial TEDRAS study revealed a notable increase in all dysphagia outcome scores in the intervention group immediately following TEE, alongside a significant increase in residue scores for all consistencies in the valleculae, and for small and large liquid boluses in the piriform sinus. These findings align with Grimm et al. [41], who identified residue as the most common dysphagia symptom in patients post-intraoperative TEE. Additionally, a prospective randomized trial by Chin et al. [24] confirmed that prolonged intraoperative TEE placement in the esophagus negatively impacts swallowing in cardiac patients. However, the initial TEDRAS trial did not evaluate the effect of TEE duration on swallowing. Based on the TEE probe’s diameter, weight and the anatomical proportions of the human oral cavity and tongue, it was hypothesized in the initial trial that the probe exerts excessive pressure on the oral, pharyngeal and laryngeal tissues, impairing the motility of the tongue, tongue base, pharyngeal wall, larynx and upper esophageal sphincter. Lastly, the initial TEDRAS study did not investigate the influence of anaesthesia on swallowing. The aim of the TEDRAS 2 follow-pp study is to address the above-mentioned limitations of the initial TEDRAS study in order to determine which factors are leading to dysphagic symptoms after TEE and thus to ensure a good aspiration prevention for stroke patients undergoing TEE.

### Oversight and monitoring

#### Trial management group

The trial management group (TMG) of the coordinating centre, Department of Neurology of the UKGM, includes the PI, key clinical investigators (MDs and SLTs as well as members of nurse staff) and non-clinical investigators (study nurse). The PI from the Department of Neurology at UKGM monitors data collection, data confidentiality, adverse events reporting and data analysis. Any adverse or unexpected events wil be promptly reported to the research project lead and to the Ethics Committee of the JLU. The trial´s dialy operations and management are overseen by the responsible MD and SLT from the Department of Neurology at UKGM. The MDs form the Department of Cardiology are responsible for the trial related conduct of TEE and report of any relevant trial related events to the PI. The TMG meetings are scheduled four times annually.

#### Trial steering committee

The Trial Steering Committee (TSC) includes independent medical experts in stroke management and a cardiologist acting as chairpersons and a statistician. The main task of TSC is to offer an independent oversight of the trial as a whole and to offer guidance through the independent chairperson. The TSC bears the final responsibility whether to continue the trial at any point of time.

#### Risks, burdens and benefits

Both interventions, FEES and TEE, are conducted according to national and international guidelines [42–46]. The additional FEES may improve the detection and, if necessary, treatment of dysphagia. Furthermore, the results of the study may help to improve the diagnosis and treatment of swallowing disorders in other patients in the future.

#### Modification and inquiry

Any modification of the study protocol will be submitted for amendment to the Ethics Board of JLU.

#### Confidentialty

All personal data recorded in the consent form and case report form will be anonymized and pseudonomized and saved in a secured database. Monitoring of research data will be conducted by the PI and may only be accessed by authorized members of the trial team.

#### Dissemination policy

The findings of the trial will be disseminated to peer-reviewed scientific journals and presented at scientific conferences.

### Trial status

This protocol is presented in #1 version, 01.12.2024. The patient recruitment has started in December 2024. Trial completion is planned for January 2026. 

## Data Availability

The datasets created and/or analyzed in this study are not publicly accessible but can be obtained from the corresponding author upon reasonable request.

## Abbreviations

FEES: Flexible Endoscopic Evaluation of Swallowing
TEE: Transoesophageal echocardiography
TTE: Transthoracal echocardiography
SSRS: Secretion Severity Rating Scale
YSv: Yale Pharyngeal Residue Severity Rating Scale for Valleculae
YSps: Yale Pharyngeal Residue Severity Rating Scale for Piriform Sinus
PAS: Penetration-Aspiration-Scale
FOIS-G: Function Oral Intake Scale (German Version)
NIHSS: National Institutes of Health Stroke Scale
MRS: Modified Rankin Scale
BI: Barthel Index
CCT: Cranial computed tomography
MRI: Magnetic resonance imaging
PI: Prinicipal investigator
UKGM: University Hospital Giessen and Marburg
MD: Medical Doctor
SLT: Speech and language therapist
